##### Global perceived effect

The global perceived effect scale is an 11-point scale ranging from –5 to 5, where –5 indicates vastly worse, 0 indicates no change and 5 indicates completely recovered. For all measures of global perceived effect (at baseline and in all follow up), participants will be asked: “Compared to when this episode first started, how would you describe your lower back pain these days?” A higher positive score indicates greater recovery and 9 of 12 negative scores indicate a worsening of symptoms. This outcome will be measured at baseline, after 6 weeks of treatment and 3 months after the intervention [5].

##### Kinesiophobia

The Tampa scale of kinesophobia (TSK), which was developed to measure the fear of movement due to chronic LBP, is a self-applied questionnaire consisting of 17 items. Each question has four response options (strongly disagree, disagree, agree and strongly agree) with scores ranging from 1 to 4 points, respectively. The scores of items 4, 8, 12 and 16 are inverted and the total score is the sum of the items, which ranges from 17 to 68 points. Increased scores reflect an increased fear of movement [23].

##### Flexibility

The flexibility of the posterior chain will be assessed by the 3 ° finger test. Participants will be asked to keep their knees fully extended and to flex their torsos toward the floor with their arms relaxed around the head. Individuals who can reach to less than 10 cm from the ground and who can touch the floor will be classified as having normal flexibility, and those who cannot reach beyond 10 cm from the floor will be classified as having reduced flexibility [17].

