### Outcome measures

The primary outcomes will be pain intensity and disability. The secondary outcomes will be quality of pain, quality of life, perception of overall effect, depression, flexibility and kinesiophobia. All scales and questionnaires have been translated into Brazilian Portuguese and their properties clinimetrically tested [6, 8, 19].

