#### Statistical analysis

Data normality will be tested through visual inspection of histograms. The statistical analysis of our study will follow intention-to-treat principles. Repeated measures analysis of variance (ANOVA) will be used to investigate the effect of treatment (Acupuncture vs Electroacupuncture), time (baseline, post-treatment, 3 months follow up), and interaction terms between treatment group versus time. If differences between groups were identified, the Turkey-test for multiple comparison will be conducted. Two-sided paired t tests will use for within-group comparisons (comparing baseline to follow up). If we found non-normally distributed data, we will use the Kurtosis-Wallis test. For all of these analyses, we will use the SPSS version 21 software (SPSS Inc, Chicago, Illinois).The confidence interval will be established at 95%, and the significance level at 0.05.

The relative gain (RG) with treatment will be calculated with the following equation:$$ R{G}_i=\frac{\left( Baselin{e}_i-En{d}_i\right)\times 100}{Baselin{e}_i} $$

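### Flexibility is defined only as normal or reduced at 10 cm, a two-class result that the planned ANOVA and t tests do not suit and that has less power than the distance in centimetres

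*Protocol article*

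**What the plan says.** Flexibility is one of six secondary outcomes in the protocol article (Outcome measures): "The secondary outcomes will be quality of pain, quality of life, perception of overall effect, depression, flexibility and kinesiophobia".

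The Flexibility section names the test, "The flexibility of the posterior chain will be assessed by the 3 ° finger test", and then gives two classes. The first is "Individuals who can reach to less than 10 cm from the ground and who can touch the floor will be classified as having normal flexibility". The second is "those who cannot reach beyond 10 cm from the floor will be classified as having reduced flexibility". Nothing else is said about how the result is scored.

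The Statistical analysis section states one set of methods for all outcomes:

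- between groups and over time: "Repeated measures analysis of variance (ANOVA) will be used to investigate the effect of treatment (Acupuncture vs Electroacupuncture), time", with a group-by-time interaction;
- within groups: "Two-sided paired t tests will use for within-group comparisons (comparing baseline to follow up";
- as a fallback: "If we found non-normally distributed data, we will use the Kurtosis-Wallis test" (the name is garbled; a rank test is evidently meant).

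It adds a relative gain, which is the percentage change from baseline divided by the baseline value. It does not say which outcomes the formula covers.

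**The concern.** The test yields a distance, but the only outcome derived from it is a yes/no class. Repeated measures ANOVA and paired t tests compare means of a quantitative variable, so an analyst who follows the article has a binary variable and no stated method designed for it.

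A cut at 10 cm also treats unequal changes badly. A patient who improves from 30 cm to 12 cm counts as unchanged, while one who moves from 10.5 cm to 9.5 cm counts as improved. At stake are the power and interpretability of this secondary comparison. There is also a practical risk: if the case forms follow the article and capture only the class, the centimetres cannot be recovered later.

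**Working it through.** **1. What is defined, outcome by outcome.** Pain has a 0 to 10 rating, Roland Morris a 0 to 24 total, McGill a total of up to 77, SF-36 domains 0 to 100, global perceived effect -5 to 5, and the Tampa scale 17 to 68. The Beck inventory has 21 items scored 0 to 3. Cut-offs are also given for Roland Morris (above 14) and Beck (bands), but there they interpret a score already defined. Flexibility is the only outcome with classes and no score.

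**2. The class rule at chosen distances.** On the natural reading, normal is under 10 cm, including touching the floor, and reduced is 10 cm or more.

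| Distance (cm) | Natural reading | 'and' read as a further condition |
|---|---|---|
| 0 | normal | normal |
| 5 | normal | no class |
| 9.9 | normal | no class |
| 10 | reduced | reduced |
| 15 | reduced | reduced |

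On the natural reading each distance gets exactly one class.

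**3. The plan's own figure.** The article states 33 per group, set by pain and disability, and nothing for flexibility. With n = 2(1.960 + 0.842)²(SD/difference)² at two-sided 5% and 80% power:

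- pain (2 points, SD 1.9) needs 15 per group, or 15/0.85, rounded up to 18;
- disability (4 points, SD 4.9) needs 24 per group, or 24/0.85, rounded up to 29.

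The stated 33 is somewhat larger than either. It has no bearing on the flexibility question except to fix the number of completers: 33 × 0.85 = 28.05, so 28 per arm.

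**4. Power on distance against power on class.** Assumptions, none of them from the document: normally distributed distances with equal SD, a single follow-up comparison, two-sided 5%, and a standardised difference d of 0.5 or 0.8.

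*Distance.* Two-sample t test with noncentrality d√(n/2), 54 degrees of freedom and critical value 2.005:

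- d = 0.5: 0.5 × √14 = 1.871, power 0.451;
- d = 0.8: 0.8 × √14 = 2.993, power 0.836.

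*Class.* If a proportion p₁ is normal in one arm, the other has p₂ = Φ(Φ⁻¹(p₁) + d). Power is by exact enumeration of the 2×2 table:

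| d | p₁ | p₂ | Chi-square, uncorrected | Fisher exact |
|---|---|---|---|---|
| 0.5 | 40.1% | 59.9% | 0.301 | 0.214 |
| 0.5 | 20.0% | 36.6% | 0.286 | 0.198 |
| 0.8 | 34.5% | 65.5% | 0.640 | 0.534 |
| 0.8 | 20.0% | 48.3% | 0.629 | 0.526 |

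**5. Relative efficiency of the split.** φ(z)²/[p(1 − p)], with p the share on one side of the cut:

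- p = 0.5: 0.3989²/0.25 = 0.64;
- p = 0.2: 0.2800²/0.16 = 0.49;
- p = 0.1: 0.1755²/0.09 = 0.34.

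**6. Relative gain.** The formula divides by baseline. A patient who touches the floor at baseline has a distance of 0 cm, and a class may be coded 0. In both cases the denominator is zero.

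**The case against.** The strongest reply is that the classes are only a clinical reading of a distance that is also recorded, just as the Roland Morris and Beck cut-offs interpret scores, and that a plan for ANOVA without exceptions itself implies a continuous variable. A condensed article may leave the detail to a fuller document. Part of this stands: the text never says that the distance goes unrecorded or is thrown away, and a reader should not infer that it is. But the Roland Morris and Beck cut-offs sit beside a stated score, and flexibility has none. The mismatch lies between two things the article does fix, so one of them needs rewording on either view.

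It can also be said that a rank test can be computed on two classes; with correction for ties it is the Pearson chi-square times (N − 1)/N, here 55/56. That is true for two groups at one time point. It does not cover the planned group-by-time analysis, and it would come in only after a normality check that has no meaning for a class.

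Stronger readings of the class rule do not hold:

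- The classes do not overlap, because touching the floor is simply a case of being under 10 cm.
- Exactly 10 cm is placed: a patient who stops there has not reached beyond it and is reduced.
- The gap between 0 and 10 cm appears only if 'and' is taken as a further condition, which would make the 10 cm limit pointless. The sentence is loose English and worth tidying, not evidence that patients cannot be classified.

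Finally, the power figures rest on assumed effects and contradict nothing the plan states. That is correct; they are illustrations.

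**Conclusion.** The point holds in this form: flexibility is defined only as a two-class result, and the planned methods are not suited to one. Under the assumptions in the working, using the class costs roughly 15 percentage points of power at d = 0.5 (45% to 29-30%; 20-22% with Fisher) and 20 to 21 points at d = 0.8 (84% to 63-64%; 53% with Fisher). The direction is dependable. The size depends on normal distances and on the share classed normal; patients piling up at 0 cm would weaken the normal approximation.

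A reader might conclude that most of the information is lost. That is too strong: efficiency is 0.64 at a median cut and 0.49 at a 20% cut, and falls well below half only for more lopsided splits. Nor is any primary conclusion at risk, since flexibility is one of six secondary outcomes and does not enter the sample size.

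**What to change.** - State that finger-to-floor distance in cm (0 = touches the floor) is recorded at baseline, 6 weeks and 3 months and is the analysed flexibility outcome. Analyse it under the planned between-group model, preferably adjusted for baseline distance.
- Keep the 10 cm class for description only, worded as under 10 cm (including touching the floor) versus 10 cm or more.
- Exclude this outcome from the relative-gain formula.
- If the class must remain the outcome, name a repeated-measures method for binary data instead.

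The cost is small but not nil. Assessors must write down a centimetre value, and because recruitment is under way, patients already assessed by class alone may lack one. If so, report how many.

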### Intervention

The AG will be treated with 0.20 × 15 Manufacture: Dong Bang, Source: Korea. Acupuncture needles at specific points (Table 1) for 40 minutes.The EG will be treated with 30 minutes of acupuncture, and EA stimulation will be used at 10 Hz and amplitude of up to 10 mA (individually adjusted according to the tolerance of the subject) in symptomatic points (Fig. 1) with the Accurate Pulse 585 applied for 10 minutes with direct current (intermittent).

**Fig. 1 Fig1:**
[figure not shown]
Flow diagram of study design showing the randomization of participants. Patients will receive 12 sessions of Chinese acupuncture or electroacupuncture treatment lasting one hour, twice a week for 6 weeks

The treatments in both groups will be administered over 6 weeks (twice a week for 12 treatment sessions) by a physiotherapist acupuncturist with experience. All patients will be directed not to seek any other type of care or treatment for their LBP for the duration of this study; they will be allowed to maintain their regular activities, which will be also monitored throughout the treatment sessions. Patients will be instructed to stay in the lateral decubitus position and to wear comfortable clothing for treatment.

### Data analysis

The sample size calculation will be performed to detect a difference of 2 points in pain intensity as measured by the NRS (estimated standard deviation = 1.9 points) and four points in functional disability as measured by the Roland Morris questionnaire (estimated standard deviation = 4.9 points). Specifications will be based on α = 0.05, statistical power of 80 % and follow up loss of 15%. Following these parameters, 33 patients will be placed in each group.

#### Sample size calculation

Sample size was defined in order to detect a 2-point difference between groups on the pain intensity outcome measured by the Pain Numerical Rating Scale, assuming a standard deviation of 1.9 points [23]. We also sought power to detect a 4-point difference in functional disability measured by the Roland Morris Disability Questionnaire, with an estimated standard deviation of 4.9 points [24, 25]. Power was defined as 80% for an alpha of 5% and attrition (drop-outs) of 15%. Accordingly, 33 participants per group will be needed.

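### The stated 33 per group does not follow from the printed inputs, which give about 30; the 80% target is still met, so this is a reporting error on the safe side

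*Protocol article*

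**What the plan says.** The justification appears twice in the protocol article, with the same inputs and the same result.

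- **Sample size calculation** takes pain intensity first: "Sample size was defined in order to detect a 2-point difference between groups on the pain intensity outcome". The SD given for this outcome is 1.9. Disability comes next: "We also sought power to detect a 4-point difference in functional disability measured by the Roland Morris Disability Questionnaire". Its SD is put at 4.9. The error rates and attrition follow: "Power was defined as 80% for an alpha of 5% and attrition (drop-outs) of 15" per cent. The conclusion is "Accordingly, 33 participants per group will be needed".
- **Data analysis** repeats the differences and SDs and then says: "Specifications will be based on α = 0.05, statistical power of 80 % and follow up loss of 15" per cent. It concludes: "Following these parameters, 33 patients will be placed in each group".

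Neither section names the test, the sidedness, a joint-power target or an allowance for a rank test. The only mention of sides is under Statistical analysis, for the within-group paired t tests. The Abstract confirms equal allocation, 33 and 33.

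**The concern.** Both sections present 33 as the consequence of the inputs just listed, so the claim can be checked, and the check fails. Nothing is left to an unseen document in order to test it, because every quantity that a two-sample calculation needs is printed, apart from sidedness. A reader who repeats the calculation gets a smaller number and cannot tell what produced the difference: a higher power, another test, a different success criterion or rounding up. What is at stake is whether the sample size statement can be reproduced and whether the power of the planned trial is described correctly. The adequacy of enrolment is not in doubt.

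**Working it through.** **Inputs** (Sample size calculation, repeated under Data analysis): NRS difference 2, SD 1.9; Roland Morris difference 4, SD 4.9; alpha 0.05; power 0.80; attrition 0.15. Allocation is 1:1 (Abstract). Two-sided testing is my assumption; one-sided is tried below.

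**Step 1. Normal approximation.** Per group, n = 2 × [SD × (z₀.₉₇₅ + z₀.₈₀) / difference]², with z₀.₉₇₅ + z₀.₈₀ = 1.960 + 0.842 = 2.802.

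- NRS: 2 × (1.9 × 2.802 / 2)² = 14.2, so 15.
- Roland Morris: 2 × (4.9 × 2.802 / 4)² = 23.6, so 24.

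**Step 2. Two-sample t test.** Power comes from the noncentral t with 2n − 2 degrees of freedom and noncentrality (difference/SD) × √(n/2). The smallest n reaching 80% is:

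- NRS (2/1.9 = 1.053): 16.
- Roland Morris (4/4.9 = 0.816): 25. Power is 79.1% at 24 and 80.7% at 25.

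Roland Morris therefore sets the size.

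**Step 3. Attrition of 15%.**

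| | Evaluable | n / 0.85 | n × 1.15 |
|---|---|---|---|
| Roland Morris, t | 25 | 29.4, so 30 | 28.75, so 29 |
| Roland Morris, normal | 24 | 28.2, so 29 | 27.6, so 28 |
| NRS, t | 16 | 18.8, so 19 | 18.4, so 19 |

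**Step 4. Attempt to reproduce 33.** The largest result from the stated inputs is 30. One-sided 5% moves further away: 20 evaluable on Roland Morris by the t test, and 20 / 0.85 = 23.5, so 24. Adjusting for baseline also lowers the number. With an assumed baseline correlation r of 0.3 to 0.5, 23.56 × (1 − r²) / 0.85 runs from 25.2 to 20.8. So 33 is not reproduced. The gap is 33 − 30 = 3 per group, or 6 of 66 (about 9%); against the lowest convention it is 33 − 28 = 5 per group.

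**Step 5. What 33 provides.** 33 × 0.85 = 28.05, so 28 evaluable per group. At two-sided 5%, t test:

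- Roland Morris: noncentrality 0.816 × √14 = 3.05, power 85.1% (86.3% by the normal approximation).
- NRS: noncentrality 1.053 × √14 = 3.94, power 97.2%.

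**Step 6. Unstated inputs that reach or approach 33.**

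- 85% power on Roland Morris: 28 evaluable, and 28 / 0.85 = 32.9, so 33.
- 90% power on Roland Morris with no attrition allowance: 33.
- 80% power with a rank-test allowance at an assumed relative efficiency of 0.864: 24 / 0.864 = 27.8, so 28, and 28 / 0.85 gives 33. Starting from 25 instead, 25 / 0.864 = 28.9, so 29, and 29 / 0.85 = 34.1, so 35.
- 80% joint power on both outcomes, assuming independence: 27 evaluable (81.0%), and 27 / 0.85 = 31.8, so 32.

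Each route either changes a stated input or adds one that the article does not give.

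**The case against.** The strongest reply is that 33 exceeds 30, so the promise of 80% power at 5% with 15% loss is kept for both primary outcomes. The 80% is a design target rather than a report of achieved power. This stands, and it limits the point to reporting. A reader might infer from the mismatch that the trial is underpowered or that the 80% claim is false. The article's own figures show the opposite.

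A second reply is that the article names no test and Statistical analysis plans a rank-based fallback, so a rank-test allowance may explain 33. It may, but it needs an efficiency figure that is not in the article, and it gives 33 from one starting value and 35 from the other. It does not rescue the statement that 33 results from the listed parameters. It does show that 85% power is only one of several explanations. Because 85% reproduces 33 exactly, a reader might take it as the true target, but nothing in the article says so.

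A reader might also infer that 33 is too few because two primary outcomes share one 5% level. The article adopts no split of alpha. It states 5% throughout and does not say that success on either outcome alone would count. Testing the calculation against a divided alpha would judge it by a rule that the plan does not contain.

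Finally, an article condenses a fuller protocol, so omitting the method is ordinary. That is true of an omission. Here the inputs and the result are both printed and do not agree.

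**Conclusion.** The point holds as a reporting error on the safe side. The printed inputs give about 30 randomised per group (28 to 30 by convention), not 33. The surplus over 30 is 3 per group, 6 in total. At two-sided 5% with 28 evaluable per group, power is about 85% for Roland Morris and 97% for NRS, so the 80% target is met as a minimum.

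This rests on a two-sided two-sample comparison of means, equal allocation, and the stated SDs and attrition. No choice of sidedness, approximation or attrition convention at 5% alpha and 80% power reaches 33. Which further input or method produced 33 cannot be determined from the article.

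**What to change.** Keep 33 per group. In both Data analysis and Sample size calculation, state that Roland Morris drives the size, and then do one of two things:

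1. Report the power that the planned number gives, for example: Roland Morris requires 25 evaluable per group for 80% power at two-sided 5%, about 30 randomised with 15% attrition; the planned 33 per group (28 evaluable) give about 85% power for Roland Morris and 97% for NRS, each at two-sided 5%.
2. If a further input or method was used, state it so that 33 can be reproduced.

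Do not write 85% as the design target unless the trial's records show that it was. The cost is a few sentences, with no change to enrolment, analysis or conduct.

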#### Statistical analysis

Data normality will be tested through visual inspection of histograms. The statistical analysis of our study will follow intention-to-treat principles. Repeated measures analysis of variance (ANOVA) will be used to investigate the effect of treatment (Acupuncture vs Electroacupuncture), time (baseline, post-treatment, 3 months follow up), and interaction terms between treatment group versus time. If differences between groups were identified, the Turkey-test for multiple comparison will be conducted. Two-sided paired t tests will use for within-group comparisons (comparing baseline to follow up). If we found non-normally distributed data, we will use the Kurtosis-Wallis test. For all of these analyses, we will use the SPSS version 21 software (SPSS Inc, Chicago, Illinois).The confidence interval will be established at 95%, and the significance level at 0.05.

The relative gain (RG) with treatment will be calculated with the following equation:$$ R{G}_i=\frac{\left( Baselin{e}_i-En{d}_i\right)\times 100}{Baselin{e}_i} $$

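### The intention-to-treat promise is not met by the named repeated-measures ANOVA, which in its classical SPSS form keeps only patients with all three visits

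*Protocol article*

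**What the plan says.** The relevant statements are all in the protocol article, under Data analysis.

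- Principle (Statistical analysis): "The statistical analysis of our study will follow intention-to-treat principles".
- Main method (Statistical analysis): "Repeated measures analysis of variance (ANOVA) will be used to investigate the effect of treatment", with the further factors "time (baseline, post-treatment, 3 months follow up), and interaction terms between treatment group versus time".
- Within-group tests (Statistical analysis): "Two-sided paired t tests will use for within-group comparisons (comparing baseline to follow up").
- Software (Statistical analysis): "For all of these analyses, we will use the SPSS version 21 software".
- Expected loss (Sample size calculation): "Power was defined as 80% for an alpha of 5% and attrition (drop-outs) of 15" per cent. The opening paragraph of Data analysis gives the same percentage.

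The section names no imputation, no mixed or likelihood-based model, and no other means of keeping a patient with a missing visit in the ANOVA. The rank test named as a fallback for non-normal data does not supply a missing score either.

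**The concern.** Classical repeated-measures ANOVA works on one complete row of scores per patient. The SPSS repeated-measures procedure removes any patient whose row has a gap. With three visits in the model, a patient who completes treatment and is assessed at 6 weeks but misses the 3-month visit is removed altogether, and the observed 6-week score goes too.

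The plan therefore states a principle that covers all randomised patients and names a method that, run in its usual form, covers completers. It also expects a loss large enough for the difference to matter.

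Two things are at stake. The first is observed data on both primary outcomes, pain intensity and disability. The second is the protection that randomisation gives to the between-group comparison. Study limitations says that participants and therapist cannot be blinded, and both primary outcomes are reported by the patient. A patient's decision to stay could therefore depend on the response in a way that differs between the arms.

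**Working it through.** **Inputs.** From Sample size calculation: 33 per arm (66 in total), attrition 15%, alpha 5%, power 80%; pain NRS difference 2 with SD 1.9; Roland Morris difference 4 with SD 4.9. From Statistical analysis: three visits in the ANOVA. Sidedness is not given in the sample-size text; two-sided is assumed.

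**1. The plan's own sample size.** n per arm = 2(1.960 + 0.842)² × (SD/difference)².
- Roland Morris: 2 × 7.85 × (4.9/4)² = 23.6, so 24; 24/0.85 = 28.2, so 29. The t-based version gives 25, then 30.
- NRS: 2 × 7.85 × (1.9/2)² = 14.2, so 15; 15/0.85 = 17.6, so 18. The t-based version gives 16, then 19.

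The stated 33 is 3 to 4 above the larger requirement. It errs on the safe side, is a separate matter and does not affect this point.

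**2. Patients analysed under complete-case ANOVA.** Per arm 33 × 0.85 = 28.05, about 28. In total 66 × 0.85 = 56.1, about 56; excluded 66 × 0.15 = 9.9, about 10.

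**3. Observed 6-week scores discarded.** The article does not say when the 15% is lost. If all loss occurs before 6 weeks, the number is 0. If all occurs between 6 weeks and 3 months, it is about 10.

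**4. Power.** Power = Φ(difference / (SD × √(2/n)) − 1.960).
- Roland Morris, n = 28: 4 / (4.9 × √(2/28)) = 3.054; Φ(1.094) = 86.3% (t-based 85.1%).
- Roland Morris, n = 33: 91.2% (t-based 90.4%).
- NRS, n = 28: 97.6% (t-based 97.2%).
- NRS, n = 33: 99.0% (t-based 98.8%).

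Both outcomes stay above the planned 80%, because recruitment was inflated for attrition.

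**5. Size of a possible bias.** The article gives nothing on how dropouts differ from completers, so these are illustrations.
- *Arithmetic.* Let the 15% lost from one arm be g Roland Morris points worse than those who stay, with random loss in the other arm. The whole-arm mean is 0.85m + 0.15(m + g) = m + 0.15g, where m is the completers' mean. For g from 0 to 4 the shift runs from 0 to 0.6 points, at most 0.6/4 = 15% of the 4-point target.
- *Simulation.* Assumptions: SD 4.9, correlation 0.6 between visits, no true effect, about 15% lost before month 3 with the chance of loss depending on the post-treatment score, 300 repetitions. With opposite dropout patterns in the two arms, complete-case analysis was off by about 1.0 Roland Morris point at month 3 (Monte Carlo SE 0.08); a likelihood analysis of all available scores was off by about 0.03. With the same pattern in both arms neither showed material bias (0.11 and 0.14, Monte Carlo SE about 0.07).

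The simulated loss depends only on a score that was observed, which is the situation in which a likelihood analysis works.

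**The case against.** The strongest reply is that the article never says that incomplete patients are dropped. It names neither the SPSS repeated-measures procedure nor a complete-case rule. Imputation before the ANOVA, or a mixed model loosely called ANOVA, would satisfy both statements. A condensed article may leave such detail to a full protocol or analysis plan that is not shown. This stands as a limit on certainty: a reader might infer that the plan prescribes a completers analysis, and the text does not go that far. It does not remove the point. The method is stated, and run in its usual form in the named software it does not deliver the stated principle.

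Other parts of the reply also stand:

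- A reader might infer that the trial loses its power. It does not; 28 per arm keeps about 85% for Roland Morris.
- A reader might infer that the result will be biased. The documents do not show this. Bias in the between-group difference arises only if loss is related to outcome differently in the two arms, and the figures of 0.6 and 1.0 rest on assumptions.
- A reader might extend the complaint to the paired t tests. A baseline-to-6-week paired test keeps a patient who is lost later, and these tests are within-group, not the randomised comparison.
- About 10 discarded 6-week records is the upper end, reached only if all loss falls after 6 weeks.
- Requiring at least one post-baseline score, as some mixed-model plans do, would still exclude patients lost before 6 weeks.

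One could also say that intention-to-treat means only analysis as allocated. That is not a full answer when about 15% of those allocated would not be analysed at all, some of them with observed primary data.

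**Conclusion.** The point holds in a limited form. Repeated-measures ANOVA in its classical SPSS form would analyse about 56 of 66 randomised patients at the planned attrition and would discard between 0 and about 10 observed 6-week records, depending on when patients are lost. That falls short of the intention-to-treat statement. The consequences are wasted primary data and a conditional risk of bias, made plausible by the unblinded design; power is not a consequence.

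The conclusion assumes that the ANOVA is run in its classical form, that nothing in an unseen document fills the missing scores, and that attrition is near the planned 15%. The change is worth making because the main analysis of both primary outcomes depends on it and it costs very little.

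**What to change.** Replace the ANOVA sentence with a likelihood-based linear mixed model for repeated measures (SPSS MIXED) with group, time and group-by-time. Use all available scores of all randomised patients, analysed as allocated. Keep baseline in the outcome vector rather than making a post-baseline score a condition of entry, so that patients lost before 6 weeks remain in the model. Report the complete-case ANOVA as a sensitivity analysis.

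The small downside is reliance on data being missing at random. Dropout that the observed scores do not predict can still bias the result, so add a sensitivity analysis for departures from that assumption.

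The cost is a few sentences in the analysis section and one additional sensitivity analysis, with the same software, visits and data and no change to the sample size. Trial status says that recruitment is under way, so the change should be fixed before outcomes are analysed.

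### Baseline is analysed as an outcome level in the repeated-measures ANOVA; if the treatment main effect decides, it carries at most two thirds of the planned difference and Roland Morris power falls below 80%

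*Protocol article*

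**What the plan says.** The Statistical analysis section of the protocol article uses repeated-measures ANOVA "to investigate the effect of treatment (Acupuncture vs Electroacupuncture), time (baseline, post-treatment, 3 months follow up" and adds the group-by-time interaction. Baseline is thus a level of the time factor, on the same footing as the two follow-ups. Three effects are listed, and none is marked as the one that answers the trial's question.

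The next step reads: "If differences between groups were identified, the Turkey-test for multiple comparison will be conducted" (taken here to mean Tukey's test). It does not say which ANOVA term or visit triggers it, or which means it compares. The only other comparisons named are within group: "Two-sided paired t tests will use for within-group comparisons (comparing baseline to follow up".

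The Sample size calculation section rests on something simpler: "Sample size was defined in order to detect a 2-point difference between groups on the pain intensity outcome", "assuming a standard deviation of 1.9 points". For disability: "We also sought power to detect a 4-point difference in functional disability measured by the Roland Morris Disability Questionnaire", with SD 4.9. Alpha is 5%, power 80%, attrition 15% and the result 33 per group. No visit, within-patient correlation or ANOVA term enters.

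**The concern.** Randomisation makes the expected group difference at baseline zero. A treatment main effect averaged over baseline and two follow-ups therefore mixes a known zero into the quantity of interest. It estimates less than the difference the trial was sized to detect.

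The trigger for the follow-up test speaks of differences between groups, which most naturally points to that main effect. On that reading the term tested is not the contrast behind the stated 80% power. A real difference in disability could be missed, and the main-effect estimate would be too small by at least a third.

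The interaction avoids the dilution. But a significant 2-df F says only that the group difference is not constant over the three visits. It gives no size, direction or visit, and the trial asks whether one technique is better than the other in the short and medium term.

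**Working it through.** **Inputs from the protocol:** NRS difference d = 2, SD 1.9; Roland Morris d = 4, SD 4.9; alpha 0.05; 33 per group; 15% loss, so 33 × 0.85 ≈ 28 completers per group; three time levels including baseline.

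**Assumptions:** a two-sided between-group test (the article says two-sided only for the paired t tests); the same SD at each visit; one common between-visit correlation ρ. The article gives no ρ, so 0.3, 0.5 and 0.7 are shown.

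**1. The plan's own figure.** n = 2(1.96 + 0.84)² SD²/d².
- NRS: 14.2, so 15 (16 with the t distribution); divided by 0.85 this is 18 to 19.
- Roland Morris: 23.6, so 24 (25 with t); divided by 0.85 this is 29 to 30.

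The stated 33 is 3 to 4 per group above the larger need, a mismatch in the safe direction. With 28 completers the simple two-group test has 97% power (NRS) and 85% (Roland Morris; SE = 4.9√(2/28) = 1.31, noncentrality 4/1.31 = 3.05, 54 df).

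**2. What the treatment main effect estimates.**
- Effect at both follow-ups: (0 + d + d)/3 = 2d/3, which is 1.33 NRS or 2.67 Roland Morris points.
- Effect at one follow-up only: d/3, which is 0.67 or 1.33 points.

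This does not depend on ρ.

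**3. Power of the treatment main effect.** The SD of a three-visit mean is SD√((1+2ρ)/3). For Roland Morris this is 3.58/4.00/4.38 at ρ = 0.3/0.5/0.7. With a sustained effect the noncentrality is 2.67/(that SD × √(2/28)) = 2.79/2.49/2.28 on 54 df.

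**4. Power of the interaction.** λ = (28/2) × S/(SD²(1−ρ)), F with 2 and 108 df. S is the sum of squared deviations of the visit-specific differences from their mean. For Roland Morris, (0, 4, 4) and (0, 4, 0) both give S = 10.67, so power is the same for a sustained and a one-visit effect: λ = 8.9/12.4/20.7.

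**5. Baseline-adjusted comparison at one visit.** The residual SD is SD√(1−ρ²), which is 4.67/4.24/3.50 for Roland Morris, with the full d retained.

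| Power, 28 per group, ρ = 0.3/0.5/0.7 | Roland Morris | NRS |
|---|---|---|
| Simple two-group test at one visit | 85% | 97% |
| Treatment main effect, sustained | 78/69/61% | 94/88/82% |
| Treatment main effect, one follow-up only | 28/23/20% | 42/35/30% |
| Interaction (either pattern) | 75/89/99% | 93/99/100% |
| Baseline-adjusted, one visit | 88/93/99% | 98/99/>99% |

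A simulation of 20,000 runs at ρ = 0.5 agrees for a sustained effect: main effect 69% and 88%, interaction 88% and 98% (Roland Morris, NRS).

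**6. Sensitivity.** With no loss at all (33 per group) the Roland Morris main effect has 85/76/68%. At ρ = 0 and 28 per group it has 93%, so the shortfall depends on the visits being correlated. To restore 80% on that term, Roland Morris would need 30/37/44 completers per group, or 36/44/52 recruited. NRS falls just below 80% only at about ρ = 0.8 (79%).

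**7. Tukey.** With two groups there is one pair, so the test repeats the F test. Over six group-by-time cells there are 15 pairs. The studentized range is then 4.08 to 4.18 (162 down to 54 df); divided by √2, the critical |t| is 2.88 to 2.95 instead of about 2.0. Roland Morris power for the 4-point difference at one visit drops from 85% to 54–57%.

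**The case against.** A reader might infer that the trial's primary test is underpowered outright. The article does not support that, for four reasons.

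- It never calls the treatment main effect the primary test, and it does list the interaction. When baseline is a time level, the interaction is the term that carries the treatment effect. For Roland Morris it reaches 80% from about ρ = 0.4, and it does not suffer when the effect is at one visit only. That removes most of the force of the 20–28% figures.
- Pain, the first-named primary outcome, keeps 82–94% even on the diluted term for a sustained effect.
- The six-cell Tukey is only one possible implementation; the two-group version is redundant but harmless.
- A condensed article may leave the primary visit and deciding contrast to an analysis plan that is not shown, so their absence alone is no finding.

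All of this stands. What remains is what the article does fix: baseline as an outcome level, a follow-up step triggered by group differences, and a sample size computed for a contrast that matches none of the listed terms. Group-by-time ANOVA is a valid test in a randomised trial, but its 2-df interaction does not estimate the 2- or 4-point difference on which the trial was sized.

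**Conclusion.** The point holds conditionally. The dilution to at most two thirds follows from randomisation and needs only the reading that the treatment main effect decides. The fall in Roland Morris power to 78/69/61% needs that reading, 28 completers per group, an effect sustained at both follow-ups and an assumed ρ of 0.3/0.5/0.7. It does not extend to NRS over that range, nor to the interaction except for Roland Morris at the low end of the range (75% at ρ = 0.3).

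The choice of method still matters whichever term was meant. For Roland Morris, using baseline as a covariate gives more power at a single visit than either listed between-group term at each correlation shown, and it estimates the difference the trial was sized on. The article's method gives up that gain although the data are already collected.

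**What to change.** Replace the ANOVA sentence with wording such as: for each primary outcome, the group difference with 95% CI at 6 weeks and at 3 months will be estimated from a linear mixed model on the two post-randomisation visits, with treatment, visit, treatment-by-visit and baseline score as terms. ANCOVA at each visit is an acceptable alternative.

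State in advance which visit is primary, and tie the 2-point and 4-point differences to that contrast. The sponsor should make this choice. The article gives no ground for preferring 6 weeks, since its Background and Discussion both stress the medium term.

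Delete the Tukey step.

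The cost is wording only. SPSS 21, the named software, fits the model, and no extra patients, visits or measurements are needed.
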